**Evaluation**

-Improvement of laboratory data about DM after surgery

-Decreasing of drug to control DM or remission of DM

**Statistical analysis**

- t-test, Chi-square test, Log-rank test, ANOVA test or Kruskal-wallis test

- HbA1c, C-peptide, lipid profile, Insulin, glucagon, IGF-1, GLP-1, Neuropeptide Y, Ghrelin, Leptin, HOMA scale: as an longitudinal data, comparing them by repeated measurement analysis of variance (RMANOVA) for comparing between Roux-en-Y gastrojejunostomy and Gastroduodenostomy

-two side p-value of less than 0.05 will be considered as statistical significance

1. Criteria for evaluation of safety, including side effects, evaluation methods and reporting methods

There are no changes in the existing surgical methods and data collection process, so there is no plan to report any postoperative complications or side effects.

1. Interim analysis

There is no planed interim analysis in this study.

1. Monitoring for data, process, and safety of this study

Investigator will do regular check.

1. Time table for the study

|  | **추진일정 (월)** | | | | | |
| --- | --- | --- | --- | --- | --- | --- |
|  | **0-1** | **2-13** | | **14-25** | **26-30** | **31-36** |
| **IRB Approval** |  |  | |  |  |  |
| **Patients’ enrollment** |  |  |  |  |  |  |
| **Data collection** |  |  |  |  |  |  |
| **Patients’ follow up** |  |  |  |  |  |  |
| **Analysis** |  |  |  |  |  |  |
| **Report** |  |  |  |  |  |  |

1. References

1) Joshua PT, David EC Cummings Hormonal and Metabolic Mechanisms of Diabetes Remission after Gastrointestinal Surgery. Endocrinology 2009 150:2518-2525

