**The mechanism of improving diabetes by surgery**

Basically reducing oral intake and nutritional absorption in GI track is a mechanism of improving hyperglycemia by surgery. In addition, various hormones such as GLP-1, IGF-1, Leptin, CCK, Ghrelin, Neuropeptide Y, which is changed its level bypassing food can lead the improvement of impairment of insulin and hyperglycemia.

1. **The upper intestinal hypothesis**

There is a theory for the improvement of hyperglycemia for patients receiving metabolic surgery: if food does not pass through duodenum (food does not contact any upper GI mucosa), an unknown-hormone which related insulin resistance, is not secreted, consequently, it can improve hyperglycemia. A study showed that duodeno-jejunal bypass (DJB) could improve DM without notable weight loss or the amount of diet. Also another study showed that excluding duodenum for food passage led improving DM, but re-including duodenum led recurrence of DM. Another study which can valid this theory showed that endoluminal duodenal sleeve which prevent the contact between duodenal mucosa and food lead improving DM.

[figure not shown]

Proximal bowel hypothesis: When excluding proximal bowel including duodenum for food passage lead improving DM (Rubino et al. Ann Surg, 2008)

1. **The lower intestinal hypothesis**

RYGB and BPD procedure makes early contacting food to distal small bowel and it lead secretion of GLP-1, one of incretin peptide and this mechanism would be related to improving DM. GLP-1 induces glucose-dependent insulin secretion and inhibits glucagon secretion, and delays gastric empting. Also, it induced increasing mass of beta-cell in *in vivo* model. GLP-1 is stimulated by nutritional contacting at L-cell in ileum and colon and induces inhibition of appetite and reducing glucose level.

[figure not shown]

Distal bowel hypothesis: early contacting food to distal part of small bowel lead secretion of GLP-1 in L-cell and it stimulate the effect of glucagon. (Rubino et al. Ann Surg. 2008)

1. **The ghrelin hypothesis**

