# Gastroduodenostomy

Gastroduodenostomy was performed using circular staple and the common channel was repaired by linear stapler after standard gastrectomy with lymphadenectomy.

Until now, no randomized controlled trial has been conducted for comparing the efficacy of DM improvement according to reconstruction type for gastric cancer surgery.

1. **Purpose**
2. Comparing the effect of improvement of hyperglycemia according to reconstruction type (Roux-en-Y gastrojejunostomy vs. gastroduodenostomy) in patients with gastric cancer and DM
3. Evaluating the mechanism of DM improvement according to reconstruction type.
4. **Place and period of the study**

Place: Severance hospital, Yonsei University College of Medicine

Periods: 2011.05.01~2014.04.30 (36 months)

1. **Selection criteria**

Inclusion criteria

1. Plan to underwent surgery for early gastric cancer, and in treatment for diagnosed DM and/or newly diagnosed DM in pre-operative check up
2. Location of tumor is lower part of stomach (possible cases of distal gastrectomy)
3. Age between 20-80
4. Understand the study and informed consent patients

Exclusion criteria

1. Patients who were treated by systemic inflammatory disease or with other malignancy
2. Uncontrolled co-morbidity
3. Vulnerable subjects (minor, pregnant women, lack of ability of recognition)
4. Severe complication after gastrectomy
5. **Sample size**

Retrospective study from our institution showed that proportion of patients who experience complete remission of DM, which was defined as no more necessity drug to control DM, was around 15% after gastroduodenostomy. It was reported that around 57% of patients who underwent Roux-en-Y gastrojejunostomy for gastric cancer with DM experienced remission of DM. Thus sample size for each group will be 18 for 0.05 of alpha and 0.20 of beta, and estimating 10% of drop-out rate, total 40 patients will be required.

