**<Methods>**

- Selecting patients who satisfy inclusion and exclusion criteria
- Randomization (without blinding):
  - Experiment arm: Roux-en-Y gastrojejunostomy
  - Control arm: Gastroduodenostomy
- Laboratory follow up: preoperation, post-operative day#7, #3months, #12 months
- Weight, fasting sugar level, post prandial 2hr sugar level, HbA1c, C-peptide (both of fasting and post prandial 2hr), lipid profile, insulin (both of fasting and post prandial 2hr), glucagon, IGF-1, GLP-1, Neuropeptide Y, Ghrelin, Leptin
- HOMA scale: HI=plasma glucose(mmol.L) x insulin(UI/ml)/22.5
- Comparing the outcomes between Roux-en-Y gastrojejunostomy and Gastroduodenostomy

1. **Variables**

-height, weight

-blood pressure, pulse rate

-duration of DM, duration of DM treatment, drug for DM

-insulin or not and amount

-pathology, postoperative morbidity and mortality

-Weight, fasting sugar level, post prandial 2hr sugar level, HbA1c, C-peptide (both of fasting and post prandial 2hr), lipid profile, insulin (both of fasting and post prandial 2hr), glucagon, IGF-1, GLP-1, Neuropeptide Y, Ghrelin, Leptin

- Laboratory follow up: preoperation, post-operative day#7, #3months, #12 months

-questionaire for quality of life

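### No planned outcome relates insulin secretion to glucose, so when resistance also differs between arms a secretion gain can be missed or look like a fall

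*Protocol*

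**What the plan says.** Under Purpose, the protocol lists "Evaluating the mechanism of DM improvement according to reconstruction type" as an aim. The background section on mechanism gives three hypotheses. The upper-intestinal one works through resistance: when food bypasses the duodenum, "an unknown-hormone which related insulin resistance, is not secreted". The lower-intestinal one works through secretion: "GLP-1 induces glucose-dependent insulin secretion and inhibits glucagon secretion". The third concerns ghrelin.

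The Methods section collects what is needed to study both resistance and secretion: "Weight, fasting sugar level, post prandial 2hr sugar level, HbA1c, C-peptide (both of fasting and post prandial 2hr), lipid profile, insulin" and further hormones, with insulin and C-peptide taken both fasting and 2 hours after a meal. It defines one derived quantity: "HOMA scale: HI=plasma glucose(mmol.L) x insulin(UI/ml)/22.5".

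The Statistical analysis section names the outcomes for repeated-measures analysis of variance between the two reconstructions: "HbA1c, C-peptide, lipid profile, Insulin, glucagon, IGF-1, GLP-1, Neuropeptide Y, Ghrelin, Leptin, HOMA scale: as an longitudinal data". Fasting and 2-hour glucose are not in that list, and no listed outcome expresses insulin or C-peptide relative to glucose.

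**The concern.** Insulin concentration depends on three things: how well the beta cell works, the glucose it is exposed to, and resistance. If glucose and resistance fall together, insulin can fall although the beta cell is working better. A raw comparison of insulin or C-peptide therefore has no fixed meaning for secretion.

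The protocol itself calls the GLP-1 effect glucose-dependent, yet the one index that uses glucose addresses resistance. At stake is the mechanistic purpose: a secretion gain after Roux-en-Y could go undetected, or a lower insulin level could be taken as a loss of secretion, when glucose values from the same visits would show otherwise.

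**Working it through.** **Inputs from the protocol.** HOMA = glucose × insulin / 22.5 (Methods), and 18 patients per arm (Sample size). There is no stated figure for the mechanism analysis. The 18 per arm does reproduce: exact enumeration of the two-sided likelihood ratio test at 0.57 versus 0.15 gives power 0.8091 and actual alpha 0.0764, and 36 / (1 − 0.10) = 40.

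**Assumptions, not in the protocol.** HOMA-beta = 20 × insulin (µU/mL) / (glucose in mmol/L − 3.5). Control arm at resistance R = 4 and beta-cell function B = 40%. Between-patient log-SD 0.35 to 0.5 for both, measurement error 10% for insulin and 3% for glucose, t-tests on the log scale.

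**Step 1: expected fasting values.** Setting G × I = 22.5R and 20I = B(G − 3.5) gives G(G − 3.5) = 450R/B, so

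G = [3.5 + √(12.25 + 1800R/B)] / 2 and I = 22.5R / G.

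- Control (R = 4, B = 40): G = (3.5 + √192.25)/2 = 8.68, I = 90/8.68 = 10.37.
- Mixed gain (R = 2.8, B = 40/0.7 = 57.1): G = (3.5 + √100.45)/2 = 6.76, I = 63/6.76 = 9.32.

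| Roux-en-Y arm relative to control | Glucose | Insulin | Insulin difference |
|---|---|---|---|
| Function +43%, resistance equal | 7.63 | 11.80 | +14% |
| Function +43%, resistance −10% | 7.35 | 11.02 | +6% |
| Function +43%, resistance −15% | 7.21 | 10.61 | +2% |
| Function +43%, resistance −20% | 7.06 | 10.19 | −2% |
| Function +43%, resistance −30% | 6.76 | 9.32 | −10% |
| Function unchanged, resistance −30% | 7.63 | 8.26 | −20% |

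Insulin is equal in the two arms at a resistance gap of about 18%. The last two rows are the difficulty: in both, HOMA is 30% lower and insulin is lower, yet only one contains a secretion gain.

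**Step 2: a second set of starting values.** Take glucose 9 and insulin 12, with glucose falling to 6.

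- Resistance-only gain: insulin 5.5, HOMA from 4.80 to 1.45, HOMA-beta unchanged.
- Secretion-only gain: insulin 18, HOMA unchanged at 4.80.
- Mixed gain: insulin 9.6 (−20%), HOMA 6 × 9.6/22.5 = 2.56, HOMA-beta from 240/5.5 = 43.6 to 192/2.5 = 76.8 (+76%).

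Insulin plus HOMA separates the first two cases. It does not give a clear reading of the third against the first.

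**Step 3: simulated trials, 18 per arm.** Ranges are over the two log-SDs.

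| Case | Raw insulin significantly higher | Raw insulin significantly lower | HOMA-beta significant |
|---|---|---|---|
| Function +43%, resistance equal | 16–28% | well under 1% | 52–81% |
| Function +43%, resistance −10% | 7–9% | under 1% | 52–81% |
| Function +43%, resistance −30% | under 1% | 13–21% | 52–81% |
| Function unchanged, resistance −30% | about 0% | 42–68% | about 5% (nominal) |

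A plain insulin-to-glucose ratio is weaker than HOMA-beta (17–30% in the mixed −30% case) but points the right way: 9.32/6.76 = 1.38 against 10.37/8.68 = 1.19. It is not free of resistance: in the resistance-only case it falls to 8.26/7.63 = 1.08.

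**The case against.** The strongest objection is that choosing a derived index is normally left to the SAP, which is not at hand, and nothing in the protocol rules one out. That lowers the weight of the point but does not remove it: the protocol names its longitudinal outcomes and defines an index for resistance only.

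Some stronger readings are tempting, and the document does not support them.

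- **That the plan judges secretion by raw insulin, or would count lower insulin against the GLP-1 hypothesis.** The protocol states no such rule. It lists variables and links none of them to a hypothesis.
- **That the hypotheses cannot be told apart.** A pure resistance gain and a pure secretion gain are separable from insulin and HOMA together, and GLP-1 itself is compared. GLP-1 is a limited rescue, because the hormone samples are drawn after an 8-hour fast while the background says GLP-1 responds to nutrient contact. The protocol also offers three contributing mechanisms, not two rivals.
- **That raw insulin will generally have the wrong sign.** This needs a resistance gap between arms of roughly 18% or more. Weight loss after gastrectomy does not by itself supply it, because both arms have gastrectomy. Below that gap the problem is lost sensitivity, not reversal.

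Two limits of the calculation also stand. The simulated data come from the HOMA model, which favours HOMA-beta. And only fasting insulin was modelled; the 2-hour insulin and C-peptide, which suit a meal-stimulated hypothesis better, were not.

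**Conclusion.** The point holds in a limited form. The protocol sets out to evaluate mechanism, describes one mechanism as glucose-dependent secretion, and lists no outcome that relates secretion to glucose. Where only secretion changes, the listed outcomes can show it, but in the assumed model raw fasting insulin does so in about 16–28% of trials against 52–81% for HOMA-beta. Where resistance is also lower in the Roux-en-Y arm, detection by raw insulin drops to 7–9% at a 10% gap and under 1% at a 30% gap; at 30%, insulin is significantly lower in 13–21% of trials despite better beta-cell function.

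These percentages rest on assumed starting values, spread and effect sizes. They show direction and rough size, not the trial's actual power. The issue concerns interpretation of the mechanistic aim only; the remission comparison and the sample size are untouched. It should be corrected, but the trial does not depend on it.

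**What to change.** In Methods, define glucose-referenced secretion indices beside HOMA, and add them to the between-arm longitudinal comparison in Statistical analysis:

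- fasting HOMA-beta = 20 × insulin (µU/mL) / (glucose in mmol/L − 3.5);
- the C-peptide-to-glucose ratio, both fasting and 2 hours post-prandial, with the 2-hour version included because the GLP-1 hypothesis is about nutrient stimulation.

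For patients on injected insulin, use the C-peptide versions. The protocol records insulin use and amount, so these patients can be identified. Keep raw insulin and C-peptide as supporting outcomes, and state that the secretion indices are read alongside HOMA resistance, since a simple ratio still moves somewhat with resistance.

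The cost is a few derived variables and a sentence or two of text, with no new samples, visits or patients. A small downside is that HOMA-beta is undefined at fasting glucose of 3.5 mmol/L or below. Although the indices could be calculated later from the stored values, naming them beforehand avoids choosing a secretion measure after the results are known.

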**Summary Statements**

Group sample sizes of 18 in group one and 18 in group two achieve 81% power to detect a difference between the group proportions of 0.4200. The proportion in group one (the treatment group) is assumed to be 0.1500 under the null hypothesis and 0.5700 under the alternative hypothesis. The proportion in group two (the control group) is 0.1500. The test statistic used is the two-sided Likelihood Ratio test. The significance level of the test was targeted at 0.0500. The significance level actually achieved by this design is 0.0764.

The formula for estimation was like as follow:

[figure not shown]

In our institution, around 50 patients underwent subtotal gastrectomy for stage I/II gastric cancer per year. Thus, 40 patients of enrollment will be possible within a year.

The duration of DM is a stratification factor for randimization and randon sequence is like as follow:

| **OBS** | **Duration of DM** | |
| --- | --- | --- |
|  | **>=5year** | **<5** |
| **1** | 1 | 2 |
| **2** | 2 | 1 |
| **3** | 2 | 2 |
| **4** | 1 | 1 |
| **5** | 2 | 2 |
| **6** | 1 | 1 |
| **7** | 1 | 2 |
| **8** | 2 | 1 |
| **9** | 1 | 2 |
| **10** | 2 | 1 |
| **11** | 1 | 2 |
| **12** | 2 | 1 |
| **13** | 2 | 2 |
| **14** | 1 | 1 |
| **15** | 1 | 2 |
| **16** | 2 | 1 |
| **17** | 1 | 1 |
| **18** | 2 | 2 |
| **19** | 2 | 1 |
| **20** | 1 | 2 |

1. **Study design and methods**

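### The named tests use neither the randomisation stratum nor the pre-operative value as an adjustment, and the RM-ANOVA term to be tested is not fixed

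*Protocol*

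**What the plan says.** **Randomisation.** Under Summary Statements: "The duration of DM is a stratification factor for randimization". Separate allocation lists follow for a duration of 5 years or more and for less than 5 years.

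**Visits.** Under Methods: "Laboratory follow up: preoperation, post-operative day#7, #3months, #12 months". The same list is repeated under Variables, so each marker has one pre-operative and three post-operative values.

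**Tests.** The Statistical analysis section lists "t-test, Chi-square test, Log-rank test, ANOVA test or Kruskal-wallis test". HbA1c, C-peptide, lipids, insulin, the hormones and HOMA are treated as longitudinal data, "comparing them by repeated measurement analysis of variance (RMANOVA) for comparing between Roux-en-Y gastrojejunostomy and Gastroduodenostomy". The threshold is "two side p-value of less than 0.05 will be considered as statistical significance".

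**Sample size.** The calculation rests on remission, not on the markers: "Thus sample size for each group will be 18 for 0.05 of alpha and 0.20 of beta", and with "estimating 10% of drop-out rate, total 40 patients will be required".

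No test is described as stratified, and no covariate is named. The section does not say what role the pre-operative value plays, whether the group or the group-by-time term is the comparison, or how an incomplete series is handled.

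**The concern.** The design collects two pieces of information that could sharpen the arm comparison, the diabetes-duration stratum and the pre-operative value of each marker. The stated analysis uses neither as an adjustment.

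For the markers, the only series the protocol describes puts the pre-operative visit in one list with the other three. Run on that series, RM-ANOVA offers two terms. The group term averages the arm difference over all visits, including one where randomisation makes the expected difference zero. The group-by-time term asks whether the arms change differently, but spreads the question over 3 degrees of freedom and yields no estimate at 12 months. Classical RM-ANOVA also needs a complete series per patient and assumes sphericity across visits spaced from one week to nine months apart.

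For remission, an unstratified chi-square test after stratified randomisation is somewhat conservative if the stratum predicts outcome.

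At stake is precision in a 40-patient trial, and a clear answer to how far the arms differ at 12 months.

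**Working it through.** **Inputs from the protocol:** 18 evaluable per arm; remission 57% against 15%; two-sided 0.05; one pre-operative and three post-operative visits; two duration strata.

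**Assumed, because the protocol gives none:** equal correlation rho between visits with a common SD of 1; the effect profile over visits; remission rates by stratum; 9 patients per arm in each stratum; missed-visit rates.

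**1. The plan's own figure.** Exact binomial enumeration of the likelihood ratio test with 18 per arm gives power 0.8091 and actual alpha 0.0764, both as printed. 36/(1 - 0.10) = 40. The figure reproduces; nothing below changes it.

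**2. Dilution of the group term.** For a constant post-operative difference D, the four-visit average is (0 + D + D + D)/4 = 0.75 D.

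**3. Power for the markers.** Effect 0.8 SD at 3 and 12 months, zero before surgery and at day 7, rho = 0.6, n = 18 per arm:

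- Group term: mean difference (0 + 0 + 0.8 + 0.8)/4 = 0.4; variance of a patient's mean (1 + 3 × 0.6)/4 = 0.70; SE = sqrt(2 × 0.70/18) = 0.279; noncentrality 0.4/0.279 = 1.43 on 34 df. Power about 29%.
- 12-month t-test: SE = sqrt(2/18) = 0.333; noncentrality 2.4 on 34 df. Power about 65%.
- 12-month ANCOVA on baseline: residual variance 1 - 0.6² = 0.64; SE = sqrt(2 × 0.64/18) = 0.267; noncentrality 3.0 on 33 df. Power 82 to 83%.
- Group-by-time: noncentrality (n/2) × sum of squared deviations of the visit differences/(1 - rho) = 9 × 0.64/0.4 = 14.4 on 3 and 102 df. Power about 89%.

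**4. Sensitivity.**

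| Scenario | Group term | Group-by-time | ANCOVA |
|---|---|---|---|
| As above, rho 0.6 | 29% | 89% | 82% (12 months) |
| 3-month effect halved, rho 0.6 | 18% | 74% | 82% (12 months) |
| As above, rho 0.4 | 35% | 72% | 72% (12 months) |
| Constant post-operative effect, rho 0.3 | 53% | 34% | 80% (post-operative mean) |
| Constant, rho 0.5 | 40% | 44% | 80% (post-operative mean) |
| Constant, rho 0.7 | 27% | 53% | 80% (post-operative mean) |

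In the last three rows the effect is set so that ANCOVA on the mean of the three post-operative values has 80% power. At rho 0.5 the variance ratio there is (0.625/0.75²)/(2/3 - 0.25) = 1.111/0.417 = 2.7.

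**5. Stratum and remission.** Pearson chi-square against Cochran-Mantel-Haenszel (CMH), the latter being [sum of (a - b)/2]² divided by the sum of 81 T(18 - T)/(18² × 17), where a and b are the remissions per arm in a stratum and T = a + b. Simulated:

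| Stratum rates: control; experimental | Chi-square power | CMH power |
|---|---|---|
| 15/15; 57/57 (not prognostic) | 79.5% | 78.9% |
| 22/8; 70/44 (moderate) | 80.0% | 80.8% |
| 28/2; 80/34 (strong) | 81.6% | 85.7% |
| 28/2; 84/30 (stronger) | 82.3% | 87.7% |

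Size under the null, chi-square against CMH: 4.6% and 4.7% (15/15); 3.9% and 4.2% (25/5); 3.3% and 3.6% (28/2). In these cases CMH is itself below 5%, so little of the shortfall comes from ignoring the stratum. A clear gap needs an extreme contrast: at 60/12 it is about 2.6% against 4.8%.

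**6. Complete series.** If each post-operative visit is missed independently with probability m, 40(1 - m)³ patients are complete: 34 at m = 5%, 29 at m = 10%.

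**The case against.** A reader might infer that the plan declares the pre-operative value to be a level of the repeated factor, that the group term is the test, and that incomplete patients are deleted. The protocol states none of these. The first is the natural reading of the visit list, the second is open, and the third is a property of the classical method rather than a rule. Details of this kind may also sit in an analysis plan that is not shown.

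Nor do the documents support saying that the analysed patients would be a non-random subset: the calculation of complete series shows a loss of numbers, not bias. They give no reason for stratifying by diabetes duration, so one cannot say that it was chosen as prognostic.

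The best defence of RM-ANOVA is that, with a pre-treatment visit in the series, group-by-time is the sensible term. It escapes the dilution, and in the first scenario above it beats 12-month ANCOVA. That stands. Its ranking reverses under other profiles, though, and it never gives the size of the difference at 12 months.

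It is also fair that ignoring the stratum is safe for type I error and usually costs little, and that a mixed model is one defensible choice among several. What remains is that the protocol fixes methods by name, collects a stratum and a baseline, and adjusts for neither.

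**Conclusion.** The point holds as an inexpensive improvement to stated methods, not as an error that invalidates the trial.

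For the markers, the loss is large if the group term on all four visits is the comparison (about 29% against 82% in the lead scenario, and 27 to 53% against 80% with a constant post-operative effect). It may be nil or reversed if group-by-time is meant. The text does not settle which.

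For remission, moving to a stratified test changes power by about -0.5 to +5 points. It does not correct an inflated error rate, because there is none from this source.

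The remission-based sample size of 40 is untouched, since remission is not among the RM-ANOVA outcomes. All power figures for the markers depend on assumed correlations and effect profiles, and those for the stratum on assumed stratum rates.

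**What to change.** **Remission:** compare the arms with a Cochran-Mantel-Haenszel test stratified by diabetes duration (<5, >=5 years), and report a stratified risk difference with its 95% CI.

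**Laboratory markers:** replace RM-ANOVA and the unadjusted comparisons by a baseline-adjusted model of the post-operative values, with the pre-operative value and the duration stratum as covariates. This can be a mixed model for repeated measures with arm, visit and arm-by-visit, which uses patients with an incomplete series, or ANCOVA at 12 months if a simpler model is preferred for about 36 patients. Name the 12-month adjusted difference as the contrast and report it with its 95% CI.

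**Cost:** a few lines of text and slightly more programming, using data already collected. If duration proves not to be prognostic, the power loss for remission is about half a point. No change to the sample size is needed.

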# Roux-en-Y gastrojejunostomy

Transecting jejunum was performed 25-30cm below treiz ligament after standard gastrectomy with lymphadenectomy. Side-to side jejuno-jejunostomy was performed 30-40cm below gastrojejunostomy.

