***Evaluation of hormonal change**

(1) blood sampling and centrifuge for plasma

Sampling at follow up point

Keep 8hr of NPO, storage in EDTA tube, centrifuge at 4℃, 1600 x g for 15 minutes. Keep plasma at -70℃

(2) Radioimmunoassay (RIA)

<commercial RIA kits>

Ghrelin과 Leptin (Linco Research, St. Charles, Missouri)

GLP-1과 NPY (Interscience Institute, Inglewood, CA)

Glucagon, IGF-1 (Endocrine Sciences Inc., Calabasas, CA)

1. **Estimated side effects of this study**

No specific additional risk

Same as standard gastrectomy

1. **Trial drop-out and stop**

When participant withdraw his/her agreement

1. **Analysis and interpretation**

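### The protocol says complications will not be reported, although it randomises the reconstruction and already collects morbidity and mortality; no comparison of harms by arm is planned

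*Protocol*

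**What the plan says.** The Methods section sets up an open randomised comparison ("Randomization (without blinding"), with "Experiment arm: Roux-en-Y gastrojejunostomy" and "Control arm: Gastroduodenostomy". The surgical description gives the experimental arm a second join in the bowel: "Side-to side jejuno-jejunostomy was performed 30-40cm below gastrojejunostomy". The control arm has a gastroduodenostomy.

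The Variables section lists "pathology, postoperative morbidity and mortality" among the data to be recorded.

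The section on criteria for evaluation of safety, whose heading covers evaluation methods as well as reporting methods, gives this reason: "There are no changes in the existing surgical methods and data collection process". It concludes: "so there is no plan to report any postoperative complications or side effects". Under Estimated side effects of this study the protocol says "No specific additional risk" and equates the risk with that of standard gastrectomy.

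The Evaluation section names only diabetes laboratory data and reduction of diabetes drugs or remission. Under Statistical analysis, the longitudinal comparison is specified for laboratory markers only. Safety monitoring consists of regular checks by the investigator. The exclusion criteria include a severe complication after gastrectomy, whereas Trial drop-out and stop mentions only withdrawal of agreement.

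**The concern.** The reason given does not lead to the conclusion drawn. Both reconstructions may be routine at the centre, but in this trial chance decides which one a patient receives, and the purpose is to compare their effect on diabetes. Any difference in complications between the arms is then a consequence of the randomised assignment. A reader deciding whether to prefer one reconstruction for its metabolic effect needs to see that difference beside the diabetes result.

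The protocol also pulls in two directions: it collects morbidity and mortality, then states that complications will not be reported. This is a stated decision and not a detail left open for a statistical analysis plan. On the plain reading of the sentence, an analysis plan that tabulated complications would depart from the protocol.

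**Working it through.** **1. The sections side by side**

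| Protocol section | Content on harms |
|---|---|
| Methods | Reconstruction assigned by open randomisation |
| Variables | Morbidity and mortality recorded |
| Selection criteria | Severe complication after gastrectomy is an exclusion; time of application not stated |
| Estimated side effects | No specific extra risk expected relative to standard gastrectomy |
| Evaluation | Diabetes outcomes only |
| Statistical analysis | General list of tests; repeated-measures analysis for laboratory markers |
| Criteria for evaluation of safety | Complications and side effects will not be reported |

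The data would exist by arm. No section says they will be compared or shown by arm, and one says they will not be reported. The statement on expected side effects compares the trial with standard surgery; it does not compare one arm with the other.

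**2. The exclusion criterion**

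Reconstruction belongs to the same operation as the gastrectomy. A severe complication after gastrectomy would therefore ordinarily become known only after the assigned procedure, although the Methods list selection before randomisation. If the criterion is applied after assignment, the patients with the most serious events leave the study, and a later table could miss them. The protocol does not settle when it applies.

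**3. What a by-arm table could show**

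The Sample size section gives 18 per arm and 10% drop-out: 36 / 0.90 = 40 in total, or 20 per arm, as the protocol states. Its power output for 57% versus 15% remission (power 0.8091, actual alpha 0.0764) also reproduces exactly by enumerating the likelihood ratio test. Those figures concern remission and say nothing about harms.

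Zero events in one arm of 20:
- one-sided 95% upper limit: 1 − 0.05^(1/20) = 13.9%
- upper end of the exact two-sided 95% interval: 1 − 0.025^(1/20) = 16.8%

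The protocol gives no complication rates, so the rates below are assumptions. Approximate 95% half-width for the difference between two arms of 20 with a common rate p is 1.96 × √(2p(1 − p)/20):

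| Assumed p | Half-width (percentage points) |
|---|---|
| 5% | 1.96 × √0.00475 = 13.5 |
| 10% | 1.96 × √0.00900 = 18.6 |
| 20% | 1.96 × √0.01600 = 24.8 |

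Power of a two-sided 5% Fisher test with 20 per arm, by exact enumeration:

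| Assumed rates | Power |
|---|---|
| 5% vs 10% | 1.7% |
| 10% vs 20% | 7.2% |
| 10% vs 30% | 24.2% |

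A formal safety test would therefore have little value. Counts with exact intervals are what these data can support.

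**The case against.** The strongest defence has four parts.

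- **Both operations are accepted.** The background calls both reconstructions common and says that reconstruction type is not related to prognosis, which fits the view that the trial adds no risk. This explains the sentence but does not justify it: prognosis is not postoperative morbidity, and the randomised contrast is between the two reconstructions.
- **Reporting may have a narrow meaning.** The sentence could mean only that no special adverse-event reporting procedure is set up. The text does not exclude this, so one should not infer an intention to withhold harms from the publication. But the heading also covers evaluation, and no other section plans a by-arm safety evaluation, so the gap remains on either reading.
- **The data would exist.** Morbidity and mortality are recorded, the Methods mention comparing outcomes between the arms in general terms, and a chi-square test is listed. This stands. A reader might infer that the trial cannot measure harm, or that an excess of complications would go unseen. The documents do not support that: the trial is single-centre and unblinded, records these events, and has the investigator checking safety.
- **The trial is too small to compare harms.** This stands as an argument against a formal test, but not against showing the counts.

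Two further inferences should be resisted. The 13.9% limit is a bound for a single arm with no events; it says nothing about a difference between arms and does not show added risk. Nor does the additional jejuno-jejunostomy establish that the experimental arm is riskier. The background's remark on tumour location and surgeon preference concerns the extent of gastrectomy and does not bear on this point.

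**Conclusion.** The point holds as a defect of planned analysis and reporting. The protocol randomises the reconstruction, collects morbidity and mortality, plans no comparison of them by arm, and states that complications will not be reported. If that is followed, a diabetes benefit would be presented without the matching harm data already in hand.

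No efficacy estimate, sample size or error rate is affected. The achievable precision is low, about 14 to 25 percentage points either side of a difference for assumed common rates of 5% to 20%, so the remedy is descriptive. The conclusion rests on the protocol alone and on reading the safety sentence in its ordinary sense; on the narrow sense, the missing by-arm evaluation still needs to be supplied. The documents contain no complication rates, so they give no ground for calling the expected-risk statement false. It needs to be reconciled with the randomised comparison.

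**What to change.** Replace the sentence in the section on criteria for evaluation of safety with text such as:

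*Postoperative morbidity and mortality, as collected, will be tabulated by assigned arm for all randomised patients, with counts and exact 95% confidence intervals, as a descriptive comparison.*

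Then reconcile two other places with it:

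- **Estimated side effects of this study:** make clear that the statement compares the trial with standard gastrectomy and does not assume equal complication rates in the two arms.
- **Selection criteria:** state when the exclusion for severe complications applies, and ensure that any randomised patient with such an event is counted in the table under the assigned arm.

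The cost is one descriptive table, which will be imprecise with about 20 patients per arm. The variables are already listed for collection. The protocol names no grading scale, and the table as worded needs none.
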